#### 10.1.4 DEFINITION OF UNANTICIPATED PROBLEMS

**Non-serious Unanticipated problems (UP):** An UP that is not an Adverse Event (UP non AE) is an unanticipated problem that does not fit the definition of an AE, but which may, in the opinion of the investigator, involve risk to the participant, affect others in the research study, or significantly impact the integrity of research data. Such events would be considered a non-serious UP. For example, accidental destruction of study records or samples.

**Serious Unanticipated problems** include any incident, experience, or outcome that meets all of the following criteria:

- Unexpected in terms of nature, severity, or frequency of what is stated under adverse events in the protocol informed consent and Investigator's Brochure.
- Related or possibly related to vaccination
- Suggests that participants or others will be at a greater risk of harm (including physical, psychological, economic, or social harm) than was previously known or recognized.

---

### 10.2 CLASSIFICATION OF AN ADVERSE EVENT

---

#### 10.2.1 SEVERITY OF EVENT

**Grading the Severity of Adverse Events:** The FDA Guidance for Industry (September 2007): "Toxicity Grading Scale for Healthy Adult and Adolescent Volunteers [Participants] Enrolled in Preventive Vaccine Clinical Trials" is the basis for the severity grading for most of the AEs in this protocol.

See [Table 8. Grading scale of AE: Clinical Abnormalities](#).

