## 4. OBJECTIVES

### 4.1 PRIMARY OBJECTIVES

- To demonstrate non-inferiority of OCV-S compared to Shanchol™ as measured by seroconversion rates of anti-*V. cholerae* O1 Inaba and anti-*V. cholerae* O1 Ogawa vibriocidal titer 2 weeks after second dose for all ages (*i.e.*, one lot of OCV-S)
- To assess and compare safety profile in all age strata combined and describe the safety profile in each age stratum 7 days and 28 days after each dose

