#### 7.2.5 ELIGIBILITY CRITERIA

##### **Inclusion Criteria**

To be eligible to participate in this study, any individual must meet the following criteria:

- Healthy participants 1 to 40 years of age at enrollment
- Participants/Parent(s)/LAR willing to provide written informed consent to participate study voluntarily
- Participants/Parent(s)/LAR who can be followed up during the study period and can comply with the study requirements

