### **Grading the Severity of Adverse Events.**

The following guidance will be used to assign a severity grade:

**Grade 1 (Mild):** No effect on activities of daily living

**Grade 2 (Moderate):** Some interference with activity not requiring medical intervention

**Grade 3 (Severe):** Prevents daily activity and requires medical intervention

**Grade 4 (Potentially Life-threatening):** Hospitalization; immediate medical intervention or therapy required to prevent death.

**Grade 5 (Death):** Death is assigned a Grade 5 severity.

Only the single AE that is assessed as the primary cause of death should be assigned “Grade 5” severity.

---

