## 13.2 SAMPLE SIZE

The sample size of the study is calculated to provide about 90% power to show primary Immunogenicity objective of immune non-inferiority of OCV-S to Shanchol™ and secondary immunogenicity objective of immune equivalence of three lots of OCV-S of the study and increased to satisfy total safety population of about N=2,530. The given sample size of N=935 participants per OCV-S and Comparator vaccine group in all ages would provide 99% power to detect the non-inferiority of immunogenicity of OCV-S group (Group C) compared to Shanchol™ (Group D) in terms of seroconversion rate. The assumed seroconversion rate of Shanchol™ is 71% for all ages which is considered in the assumption based on the clinical studies conducted in a neighboring country to Nepal (i.e., India). The sample size of N=330, 360, and 245 participants per OCV-S and Shanchol™ would provide 80% power to detect non-inferiority of OCV-S in terms of seroconversion rates of 75%, 71%, and 84% in adults, adolescents, and young children, respectively. The assumed non-inferiority margin is -10% based on WHO TRS 924. One sided test of non-inferiority is used with significance level of 0.025.

The sample size of N=330 per lot of OCV-S in adults will also provide >90% power for three equivalence tests of GMT ratio of immunogenicity among three lots of OCV-S (A vs. B, B vs. C and C vs. A) with overall two-sided significance level of 0.05. Each of two-sided equivalence test have >90% power to show the equivalence of GMT of immunogenicity of OCV-S with two-sided significance level of 0.05. The equivalence margin of ratio was assumed as [0.5, 2.0] according to precedent study of OCV (i.e., Euvichol®) and other oral vaccine trials, the true GMT ratio is assumed as 1 and the coefficient of variation on titer of immunogenicity is assumed as 2.0. The coefficient of variation of GMT of OCV-S was assumed conservatively based on OCV immunogenicity data. In both sample size calculations, 10% drop out rate is assumed conservatively considering the potential large variation of experience between sites.

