| Diarrhea                                                                                                                                                                                                                                                                                                                                                                                               | 2-3 loose stools or < 400 gms/24 hours                 | 4-5 loose stools or 400-800 gms/24 hours                                                 | 6 or more watery stools or > 800 gms/24 hours or requires outpatient IV hydration | ER visit or Hospitalization                       |
| Headache                                                                                                                                                                                                                                                                                                                                                                                               | No interference with activity                          | Repeated use of non-narcotic pain reliever > 24 hours or some interference with activity | Significant; any use of narcotic pain reliever or prevents daily activity         | ER visit or Hospitalization                       |
| Fatigue                                                                                                                                                                                                                                                                                                                                                                                                | No interference with activity                          | Some interference with activity                                                          | Significant; prevents daily activity                                              | ER visit or Hospitalization                       |

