| Respiratory Rate - breaths per minute                                                                                                                                                                                                                                                                                                                                                                                                                                                                                                                                                                                                                      | 17-20                    | 21-25                     | > 25                     | Intubation                                    |
| a In addition to grading the measured local reaction at the greatest single diameter, the measurement should be recorded as a continuous variable.
b Induration/Swelling should be evaluated and graded using the functional scale as well as the actual measurement.
c Participant should be at rest for all vital sign measurements.
d No recent hot or cold beverages or smoking.
e When resting heart rate is between 60-100 beats per minute. Use clinical judgment when characterizing bradycardia among some healthy participant populations, for example, conditioned athletes. |                          |                           |                          |                                               |

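### Severity at ages 1-40 is graded mostly on an adult and adolescent scale with no age-specific vital-sign limits, and its diarrhoea criteria can give one episode two grades

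*Protocol*

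**What the plan says.** Protocol section 10.2.1 names the source of the grades, "Toxicity Grading Scale for Healthy Adult and Adolescent Volunteers [Participants] Enrolled in Preventive Vaccine Clinical Trials", and says that this "is the basis for the severity grading for most of the AEs in this protocol". The same section then gives a general functional scale, introduced by "The following guidance will be used to assign a severity grade", which runs from no effect on daily life to death and is not tied to age.

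Table 8 (Appendix I) sets out the cut-offs. It has no paediatric column and no age footnote.

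- The row "Respiratory Rate - breaths per minute" gives Grade 1 at 17-20, Grade 2 at 21-25 and Grade 3 above 25.
- Tachycardia is Grade 1 at 101-115, Grade 2 at 116-130 and Grade 3 above 130. The bradycardia footnote takes a resting pulse of 60-100 as its reference.
- Diarrhoea is Grade 1 at "2-3 loose stools or < 400 gms/24 hours". Grade 3 is met by six or more watery stools, by more than 800 g, or by outpatient intravenous hydration.

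The inclusion criterion is "Healthy participants 1 to 40 years of age at enrollment". A primary objective (section 4.1) is to "describe the safety profile in each age stratum 7 days and 28 days after each dose". Section 13.6.4 places a tabulation by maximum severity within the primary safety analysis.

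**The concern.** The scale's own title stops at adolescence, but the protocol applies it unchanged down to age 1. Two consequences follow from the text.

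First, if a vital-sign change in a young child is reported as an adverse event, its grade comes from limits with no age adjustment. The grade then partly reflects the child's age, not the severity of the event.

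Second, the 'or' between stool count and stool mass lets a single episode satisfy two grades, and nothing says which one prevails. The maximum-severity table does not settle this. It takes the highest of the grades assigned to a participant's events, but each episode must first be given one grade.

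At stake is how far the severity breakdown can be trusted in the youngest participants, and whether severity can be compared across strata or pooled over them.

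**Working it through.** The plan gives no figure on severity grading to reproduce. The stratum sizes were checked first, then each part of Table 8.

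**1. Who is affected.** Section 13.2 plans "N=330, 360, and 245 participants per OCV-S and Shanchol™" for ages 18-40, 6-17 and 1-5. Groups A and B add 330 adults each (Table 1).

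- Total: 330 + 330 + 2 × (330 + 360 + 245) = 2,530, as stated.
- Ages 1-5: 2 × 245 = 490, and 490 / 2,530 = 19.4%.
- Ages 6-17: 2 × 360 = 720. How many are below adolescence is not stated; appended Table S2 gives a median age of 10 years in this stratum.
- All under 18: 490 + 720 = 1,210, or 47.8%.

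**2. Diarrhoea, two grades at once.** Take six watery stools in 24 hours with a mass below 400 g. The mass alternative meets Grade 1; the count alternative meets Grade 3. This does not depend on age.

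**3. Diarrhoea, stool mass against body size.** Mean weights from Table S2 are 56.80 kg (18-40), 32.74 kg (6-17) and 14.27 kg (1-5). Dividing each mass limit by mean weight:

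| Stratum | 400 g | 800 g |
|---|---|---|
| 18-40 | 7.0 g/kg | 14.1 g/kg |
| 6-17 | 12.2 g/kg | 24.4 g/kg |
| 1-5 | 28.0 g/kg | 56.1 g/kg |

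The ratio of youngest to adult is 56.80 / 14.27 = 3.98. On the mass criterion alone, a child aged 1-5 needs about four times the adult loss per kg for the same grade.

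**4. Vital signs.** The documents give no normal ranges for children. Assumption: at ages 1-5, resting respiratory rate runs from 20 to an upper end of 30-40 per minute, and pulse from 80 to an upper end of 130-140.

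- Respiratory rate: 20 is Grade 1, 21-25 is Grade 2 and above 25 is Grade 3, so every value in the assumed range is graded.
- Pulse: 80-100 is ungraded, 101-115 is Grade 1, 116-130 is Grade 2, and 131-140, if the upper end is 140, is Grade 3.

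**5. Did readings become events?** In appended Table S4, 244 of 2,529 participants (9.65%) had any treatment-emergent event, at all ages and after either dose. Moderate events occurred in 68 and severe in 18, so at most 68 + 18 = 86 participants had either. Reactions within 30 minutes occurred in 4. The 1-5 stratum alone had 484 children in the full analysis set (Table S2). Out-of-band readings were therefore not turned into events automatically.

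**6. What the frequency objective needs.** Section 13.1.2 defines the primary safety endpoint as the frequency of solicited events, unsolicited events and SAEs; it does not use the grade. With 245 per group, the smallest true frequency that gives a 95% chance of seeing at least one event is 1 − 0.05^(1/245) = 1.2%. Grading does not affect this.

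**The case against.** Four arguments stand against a stronger reading.

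- **The objective survives.** A reader might infer that the safety objective in each age stratum cannot be answered. The documents do not support this. The objective is descriptive, its endpoint is frequency, and severity is an additional tabulation.
- **A reading is not an event.** A reader might infer that most healthy toddlers would be recorded with moderate or severe vital-sign events. Table 8 grades adverse events. Section 7.2.9 reports new findings as events only if clinically relevant, and vital signs are not among the solicited events in section 10.1.1. The appended counts agree. The paediatric ranges are also an assumption from outside the documents.
- **Stool mass is not collected.** Tables 6 and 7 assess events by observation, interview and diary card, and no visit procedure weighs stools. Count or hydration will usually set the grade, so the fourfold gap per kg has little practical effect. The same point softens the two-grade problem, which in any case is not specific to children.
- **The arms share the scale.** Randomisation is stratified by age (section 8.4) and no hypothesis in section 13.4 concerns severity. Misgrading is expected to be the same in both arms, so bias toward one vaccine cannot be inferred.

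It is also fair that section 10.2.1 says most events, not all, and adds a functional scale. Several Table 8 rows (fatigue, myalgia, anorexia, other illness) are purely functional and work at any age.

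These arguments limit the consequence but leave the rule as written. When a young child's vital-sign change is reported as an event, Table 8 supplies limits without age adjustment, and section 10.2.1 does not say whether the functional scale takes precedence.

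**Conclusion.** The point holds in a limited form. The protocol applies a scale titled for adults and adolescents to ages 1-40 without age-specific vital-sign limits, and its diarrhoea row can assign Grade 1 and Grade 3 to one episode. Both are visible in the text and need no outside figure.

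The affected output is the maximum-severity breakdown in section 13.6.4 for children below adolescence: the 490 planned at ages 1-5 (19.4% of 2,530) and an unstated part of the 720 aged 6-17. Severity comparisons across strata, or pooled over them, carry the same weakness. Table S4 does compare severity between vaccines over all ages (severe events in 11 participants of Group C and 3 of Group D, p = 0.0319). That is no evidence of misgrading, but it shows that the pooled grades are put to use.

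The size of any misgrading cannot be derived from the documents. That healthy toddlers' readings fall in graded bands rests on the assumed ranges, and it matters only when a reading is reported as an event. The non-inferiority and lot-consistency analyses are untouched. This is an inexpensive improvement, not a threat to the trial's main conclusions.

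**What to change.** In section 10.2.1 and Table 8:

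1. Limit the current vital-sign rows to the ages the named scale covers. For younger children, use age-banded grades from a recognised paediatric scale, cited in the protocol.
2. For those children, grade diarrhoea by stool count and by functional or hydration criteria, without the absolute-mass alternative.
3. State for all ages that the highest grade met applies.

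The cost is an appendix change, revised eCRF checks and site training. The downside is that vital-sign severity in the younger children would be on a different scale from the rest, so pooled severity tables need a footnote saying so.

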### **Grading the Severity of Adverse Events.**

The following guidance will be used to assign a severity grade:

**Grade 1 (Mild):** No effect on activities of daily living

**Grade 2 (Moderate):** Some interference with activity not requiring medical intervention

**Grade 3 (Severe):** Prevents daily activity and requires medical intervention

**Grade 4 (Potentially Life-threatening):** Hospitalization; immediate medical intervention or therapy required to prevent death.

**Grade 5 (Death):** Death is assigned a Grade 5 severity.

Only the single AE that is assessed as the primary cause of death should be assigned “Grade 5” severity.

---

### **10.2.2 RELATIONSHIP TO INVESTIGATIONAL PRODUCT**

For all collected AEs, the investigator who examines and evaluates the participant will determine the relationship of each AE with the investigational product based on plausible biologic mechanism, temporal relationship of occurrence after administration of the investigational product, identification of possible alternative etiologies including underlying disease, concurrent illness or concomitant medication, and the investigator’s clinical judgment. The relationship of vaccination to adverse event (AE) will be determined based on the definitions below.

**Definitely Related** – There is clear evidence to suggest a causal relationship, and other possible contributing factors can be ruled out. The clinical event, including an abnormal laboratory test result, occurs in a plausible time relationship to vaccine administration and cannot be explained by concurrent disease or other drugs or chemicals. The response to withdrawal of the Vaccine (dechallenge) should be clinically plausible.

**Probably Related** – There is evidence to suggest a causal relationship, and the influence of other factors is unlikely. The clinical event, including an abnormal laboratory test result, occurs within a reasonable time after administration of vaccine, is unlikely to be attributed to concurrent disease or other drugs or chemicals, and follows a clinically reasonable response on withdrawal (dechallenge).

**Possibly Related** – There is some evidence to suggest a causal relationship (e.g., the event occurred within a reasonable time after administration of vaccine). However, other factors may have contributed to the event (e.g., the participant clinical condition, other concomitant events). Although an AE may rate only as “possibly related” soon after discovery, it can be flagged as requiring more information and later be upgraded to “probably related” or “definitely related,” as appropriate.

**Unlikely to be related** – A clinical event, including an abnormal laboratory test result, whose temporal relationship to vaccine administration makes a causal relationship improbable (e.g., the event did not occur within a reasonable time after administration of vaccine) and in which other drugs or chemicals or underlying disease provides plausible explanations (e.g., the participant clinical condition, other concomitant treatments).

**Not Related** – The AE is completely independent of vaccine administration, and/or evidence exists that the event is definitely related to another etiology. There must be an alternative, definitive etiology documented by the clinician.

The criteria for determining causality can be documented as follows: The initial four definitions can be considered as ADR and the last one *i.e.* “Not Related” can be considered as Non-ADR.

---

### 10.2.3 EXPECTEDNESS

The Study Medical Monitor in consultation with site PI will be responsible for determining whether an AE is expected or unexpected. An Adverse Reaction will be considered unexpected if the nature, severity, or frequency of the event is not consistent with the risk information previously described for the study agent.

### 10.3 TIME PERIOD AND FREQUENCY FOR EVENT ASSESSMENT AND FOLLOW-UP

All participants will be observed for immediate adverse reactions for 30 minutes after each vaccination. For 7 consecutive days (Days 0-6) after each dose of study vaccine, the participant/parent(s)/LAR will be asked to record solicited symptoms in the diary card. The study staff will remind participant/parent(s)/LAR of the importance of properly filling the diary cards and to return the cards at the next scheduled study visit. If they did not fill up or lost their card, the

participant/parent(s)/LAR will be interviewed for recall of symptoms with trained study staff during clinic visit on Day 7 after vaccination.

The occurrence of an adverse event (AE) will come to the attention of study personnel during study visits and interviews of a study participant presenting for medical care, or upon review by a study monitor.

All AEs not meeting the criteria for SAEs will be captured on the appropriate case report form (eCRF). Information to be collected includes event description, time of onset, symptoms and physical examination findings, clinician's assessment of severity, relationship to study product (as assessed by the PI or delegated SI), medications given and time of resolution/stabilization of the event. All AEs occurring while on study will be documented appropriately regardless of relationship.

Changes in the severity of an AE will be documented to allow an assessment of the duration of the event at each level of severity to be performed. AEs characterized as intermittent require documentation of onset and duration of each episode.

The investigator will record all reportable events with start dates occurring any time after informed consent is obtained until the last day of study participation. At each study visit, the investigator will inquire about the occurrence of AE/SAEs since the last visit. Events will be followed for outcome information until resolution or stabilization.

## 10.4 REPORTING PROCEDURES

### 10.4.1 ADVERSE EVENT RECORDING AND REPORTING

Adverse events, solicited AEs, and SAEs will be assessed at various study visits, documented in the source record, and recorded in the eCRF using accepted medical terms and/or the diagnosis that accurately characterize the event. When the diagnosis is known the AE term recorded in the eCRF will be the diagnosis rather than constellation of symptoms. The site PI or delegated SI will assess all AEs for seriousness, relationship to investigational product, severity, and other possible causes.

The timeframe for the collection of adverse events (AEs) occurring from the first administration of investigational product through to the end of the trial and will be collected as well as recorded in the source document and eCRF according to the MOP.

All AEs will be followed until they have resolved or are considered stable during the study. When an AE has not resolved by the current visit it will be documented in the eCRF as ongoing. If the event has a resolution date, this date must be recorded on the Adverse Event form, regardless of whether it falls within the AE reporting period.

Documentation will include date of onset, detailed description of the event and relevant history and physical examination, severity, attribution of the AE, treatment given and date the AE improved or resolved. The medical monitor will review the AEs reported regularly and clarify with PI or SI if there are queries. The data manager will review all AEs for consistency and provide summary of AEs to the medical monitor periodically. Non-clinically significant AEs still ongoing as the end of the study will be listed as continuing. SAEs continuing at the end of the study will be followed to resolution or stabilization. Details of AE reporting are included in the MOP.

The PI, sub-investigators, and site staff will exercise due diligence in ascertaining, accurately recording and promptly entering data on the eCRF for all AEs of all study participants. As data becomes available from the participant, the clinic adverse events should be recorded and entered by the site staff on regular basis. Site investigators will review, in a timely manner, the AE source data and determine the severity of the event and relation to the study agent. Site investigators will contact the study medical monitor for consultation of AEs as required.

---

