#### **Home visit/Phone call 1. Post 1st dose 1-week safety follow-up (Day 7 / Week 1 $\pm$ 1 days)**

Each participant will be followed up for safety via home visit at Day 7 after the first dose of vaccination. A visiting site staff will,

- 1) Verify and collect recorded DC1 and confirm with participant/parent(s)/LAR.
- 2) Record solicited and unsolicited events and concomitant medications in DC1 in study database.
- 3) Provide DC2 to document any unsolicited adverse events (if any occurrence is there) during Day 7 to Day 13 before the next visit
- 4) Remind to bring DC2 at Visit 3 on Day 14.
- 5) Remind to visit the site for the second dose of vaccination at Day 14.
- 6) Remind the participant/parent(s)/LAR to contact investigator/ study staff if needed.

Home visit may be replaced by a phone call. Only a qualified healthcare professional (HCP) according to Nepal's definition of HCP (*i.e.*, registered physician, health assistant nurse practitioner, public health nurse, auxiliary health worker), should perform the call. A staff calling the participants will,

- 1) Check the participant's identification.
- 2) Call out all the solicited adverse events listed in DC1 to participant(s)/parent/LAR so that the adverse events can be confirmed through the call.

- 3) Enter the adverse events in DC1 into eCRF when DC1 is collected.
- 4) Instruct to document any adverse events (if any occurrence is there) during Day 7 to Day 13 in DC2 and remind to bring DC1 and DC2 at Visit 3 on Day 14.

Home visit/phone call maybe replaced by a site visit.

Each AE will be assessed according to the following method:

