#### 10.1.1 DEFINATION OF ADVERSE EVENTS

**Adverse events (AE):** These are defined as any untoward medical occurrence which follows vaccination, and which does not necessarily have a causal relationship with the administration of the vaccine. An AE may be any unfavorable or unintended sign, symptom, or disease.

**Adverse Drug Reactions (ADR):** All noxious and unintended responses to a medicinal product related to any dose should be considered adverse reactions (AR). The phrase “responses to a medicinal product” means that a causal relationship between a medicinal product and an AE is exist with at least a reasonable possibility.

**Solicited AEs** are predetermined events, identified in the Investigator’s Brochure (IB), which may reflect safety concerns related to the investigational product. AEs that will be solicited by the participant/ parents/LAR and recorded in the diary card and reviewed by a blinded observer during the 7 days after each dose for this study include fever, nausea/vomiting, diarrhea, headache, fatigue, myalgia and anorexia/loss of appetite.

**Unsolicited AEs** are all other adverse events (those that do not fall under the categories of Solicited AEs listed above) that are identified by site staff, the site investigator and the Safety Medical Monitors. These unsolicited AEs will be documented in the participant’s study records and entered in the study eCRFs.

Results will be expressed as frequency of the AEs and individual descriptions will be tabulated according to MedDRA organ class system and preferred term.

---

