#### 13.1.2 PRIMARY SAFETY ENDPOINT

- Frequency of solicited adverse events within 7 days post vaccination, unsolicited adverse events within 28 days post vaccination, and SAEs after each dose during the entire study period in all ages and in each age stratum.

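### Section 10.4.1 puts a known diagnosis in place of symptoms for solicited AEs too, against the diary-entry steps, so the solicited frequency may be understated

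*Protocol*

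**What the plan says.** - **Scope of the recording rule (section 10.4.1).** The paragraph opens with "Adverse events, solicited AEs, and SAEs will be assessed at various study visits, documented in the source record, and recorded in the eCRF". Solicited AEs are therefore named explicitly.
- **Choice of term (same sentence).** Events are recorded "using accepted medical terms and/or the diagnosis that accurately characterize the event".
- **Diagnosis rule (next sentence).** "When the diagnosis is known the AE term recorded in the eCRF will be the diagnosis rather than constellation of symptoms". It applies when a diagnosis is known and has no exemption.
- **Solicited list (section 10.1.1).** The events solicited "during the 7 days after each dose for this study include fever, nausea/vomiting, diarrhea, headache, fatigue, myalgia and anorexia/loss of appetite". Everything outside these categories is unsolicited by definition.
- **Diary entry (section 7.1.3).** At Home visit/Phone call 1, staff are told: "Record solicited and unsolicited events and concomitant medications in DC1 in study database". The phone variant has them enter the card's events in the eCRF once the card is collected. Home visit/Phone call 2 gives matching steps for the second dose and the third diary card.
- **Endpoint (section 13.1.2).** The first component of the primary safety endpoint is "Frequency of solicited adverse events within 7 days post vaccination". Unsolicited AEs within 28 days and SAEs are the other two.

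**The concern.** All seven solicited events are symptoms or signs, and a unifying diagnosis is not on the list. If the diagnosis replaces the symptoms as the eCRF term, section 10.1.1 puts the resulting event in the unsolicited category, although the underlying symptoms were solicited and began inside the 7-day window.

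The diary steps give staff a different instruction for the same event, and nothing in the protocol says which prevails. Four sites could resolve this in different ways.

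Two things are at stake. The first is the split between solicited and unsolicited frequencies, which the primary safety endpoint reports separately. The second is severity, because Table 8 grades listed symptoms and general illnesses on different scales and section 13.6.4 plans a summary by maximum severity.

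**Working it through.** The point turns on reading the sections together; no sample-size or power formula bears on it.

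**1. Follow section 10.4.1 literally.** Take a child with diarrhea, vomiting and fever on Day 2 and a known diagnosis of gastroenteritis.
- The event is a solicited AE, so it is within the paragraph's scope.
- A diagnosis is known and there is a cluster of symptoms, so the condition of the diagnosis rule is met.
- The eCRF term is gastroenteritis, which is not one of the seven listed categories, so section 10.1.1 makes it unsolicited.
- Result: 0 solicited events and 1 unsolicited event.

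**2. Follow the diary steps in section 7.1.3.** The same three symptoms are on the diary card and are entered as solicited events. Result: 3 solicited events (nausea/vomiting, diarrhea, fever).

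**3. Compare grading (Appendix I, Table 8).** Four or five loose stools in 24 hours are Grade 2 on the diarrhea row, and six or more watery stools are Grade 3. The general illness row grades by interference with activity and need for medical intervention. A child with four loose stools and undisturbed activity is Grade 2 on the first and Grade 1 on the second.

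**4. What does not change.** The participant still has a recorded AE, so the number of participants with any TEAE is the same under both readings. Only the solicited/unsolicited split, the event counts and possibly the grade move.

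**5. The document's own figure.** The appended Table S4 gives solicited AEs after any vaccination, and it reproduces:
- Total: 136/2529 = 5.38%
- Group C: 51/934 = 5.46%
- Group D: 54/934 = 5.78%
- Uncorrected chi-square, C vs D: p = 0.7631

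**6. Can the understatement be computed?** No. It needs the share *g* of participants with solicited events who left the solicited count because a diagnosis replaced all their listed symptoms, and the document does not give *g*. As an assumption only, underlying frequency = observed / (1 − *g*):

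| assumed *g* | Total | Group C | Group D |
|---|---|---|---|
| 0% | 5.38% | 5.46% | 5.78% |
| 5% | 5.66% | 5.75% | 6.09% |
| 10% | 5.98% | 6.07% | 6.42% |
| 20% | 6.72% | 6.83% | 7.23% |
| 30% | 7.68% | 7.80% | 8.26% |

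With the same *g* in both arms the C/D ratio stays at 51/54 = 0.94. Nothing in the document favors any row over *g* = 0.

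**The case against.** The strongest defense is that the two instructions can both be met. Solicited AEs have their own route: they are predefined, recorded by the participant or parent for seven days, checked at a scheduled contact, recovered by interview if the card is lost (section 10.3), and entered in the database. No section says that a diary symptom is deleted or reclassified once a diagnosis is made. Section 10.3 also keeps symptoms among the items collected for an AE. The wording just before the diagnosis rule allows medical terms as well as diagnoses, the rule is conditional, and section 10.4.1 leaves further detail to the MOP, which is not shown.

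Much of this stands. It means the loss of solicited events is possible, not established. It does not remove the conflict: the diagnosis sentence is specific to the case where a diagnosis is known, it says the diagnosis is recorded instead of the symptoms, and it covers solicited AEs by name. A manual that is not shown cannot be assumed to reverse it.

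A reader might infer more from four places, and none of them supports it.
- **Table 2.** The solicited row is not marked at the unscheduled visit. It is not marked at Visits 2 and 3 either, where the solicited windows open. It marks the contacts at which the diary is reviewed, not which events count.
- **Table S4 after dose 2.** Solicited AEs are 15 vs 31 (C vs D) while any TEAE is 54 vs 55, which could look like reclassification. After dose 1, however, Group C is higher for both solicited (37 vs 26) and unsolicited AEs (33 vs 26), which is not a substitution pattern. The rule covers both arms.
- **Power.** Section 13.3 compares safety descriptively and sets no safety hypothesis, so there is no planned power to lose.
- **Medical attendance.** The rule depends on a known diagnosis, not on whether care was sought.

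**Conclusion.** The point holds as a contradiction in a stated rule. Section 10.4.1, read with section 10.1.1, can turn listed symptoms in Days 0-6 or 14-20 into a single unsolicited AE graded on the generic illness row, while section 7.1.3 has the same symptoms entered as solicited. The solicited frequency in the primary safety endpoint may therefore be understated, and coding may differ between sites.

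The direction rests on two conditions: a diagnosis is known within the solicited window, and the site lets the diagnosis sentence override the diary entry. The size cannot be determined from the document; the table above shows only how it would scale. It would go too far to say that the frequency is understated, that the comparison of Groups C and D is biased, or that Table S4 was affected. The document shows none of these. The change is still worth making, because the rule touches a named component of a primary endpoint and costs almost nothing to correct.

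**What to change.** In section 10.4.1, limit the sentence that puts the diagnosis in place of the symptoms to unsolicited AEs and SAEs. Then add, for example: *Each solicited symptom with onset in the 7-day window after a dose is recorded, graded on its own Table 8 row and counted under its own solicited term, whether or not a diagnosis is made. A diagnosis is entered in addition and linked to those symptoms.* Carry the same rule into the eCRF completion instructions. Table 2 needs no change.

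The cost is about two sentences, a completion note and a link field. There is one small downside: an illness may appear both as solicited symptoms and as a linked diagnosis. Counts of events must use the link to avoid counting it twice. The number of participants with any TEAE is unaffected, since each participant is counted once.
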